### Sample size

2.8

Sample size estimation was based on the primary medical outcome SMM. For the estimation, both additional groups (K1, K2) were pooled which results in a matching ratio of 2 women (S) vs. 3 women (K1 + K2). Following the multiply matched study design, a score test established on a conditional logistic regression model was used (41). The test assesses the effect of a binary variable (= with/without pre-existing medical condition) on the outcome with a variable number of cases and controls in a matched set. Assuming a SMM rate of 50 per 1,000 women in S and a SMM rate of 23/1000 in K1 + K2 257 matched sets of size 5 (2:3) are required to provide 90% power at a significance level of 5%. Considering a drop-out rate of about 15%, 1,500 women in 300 matched sets of size 5 have to be recruited.

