### Statistical analysis

2.10

All medical parameters will be summarized using descriptive statistics. The primary medical outcome will be analyzed with a conditional logistic regression model to assess the effects of pre-existing medical conditions on the SMM rate. Odds ratios obtained from this model with corresponding 95% confidence intervals will be reported. Further secondary medical maternal and perinatal parameters will be compared between the study and additional groups. Additional analyses of medical parameters will be considered in subgroups given by different pre-existing conditions in the study group and are exploratory in nature. The main analysis will be performed on complete cases and the significance level will be set to 0.05. A sensitivity analysis will include the use of multiple imputation strategies to address possible missing observations.

For analysis of costs, a health economic evaluation to determine the costs associated with the interventions and services in the different groups will be conducted. This includes, for example, consultation time, laboratory tests, medical procedures, hospitalization, or medication. The resource use of implemented care of all the three groups will be captured, both for inpatient and outpatient setting. Thereafter, this resource use will be multiplied times unit prices to derive respective costs from a provider (in-and outpatient healthcare provider) and healthcare system perspective (statutory health insurance).

The items of the questionnaires will be summarized descriptively at each time point. Health-related quality of life will be analyzed as pre-specified in the manual of the EQ-5D-5L™ tariff and compared over time (42). The birth experience assessed by the German version of the BSS-R will be reported via the total score and the three subscales (stress during labor, personal attributes, and quality of care provision) (39).

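### The stated inputs do not give 90% power at 257 matched sets: about 74% if the test is two-sided, about 83% if one-sided

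*Protocol article*

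**What the plan says.** Section 2.8 (Sample size) of the protocol article sizes the study on the primary medical outcome, SMM. The inputs are "Assuming a SMM rate of 50 per 1,000 women in S" and "a SMM rate of 23/1000 in K1 + K2", with "a matching ratio of 2 women (S) vs. 3 women (K1 + K2") in each set. For the method, "a score test established on a conditional logistic regression model was used". The result is that "257 matched sets of size 5 (2:3) are required to provide 90% power at a significance level of 5" per cent. The recruitment target follows: "Considering a drop-out rate of about 15%, 1,500 women in 300 matched sets of size 5 have to be recruited".

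The section gives neither the sidedness of the 5% level nor any within-set correlation.

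Section 2.10 (Statistical analysis) uses the same model for the primary analysis: "The primary medical outcome will be analyzed with a conditional logistic regression model". It adds that "Odds ratios obtained from this model with corresponding 95% confidence intervals will be reported" and sets the significance level at 0.05.

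**The concern.** The event counts look too small for the power claimed. At the planned rates, 257 sets hold 514 S women and 771 K women. That gives about 26 expected SMM cases in S (514 × 0.050 = 25.7) and about 18 in K1 + K2 (771 × 0.023 = 17.7). A conditional analysis uses only sets with at least one case and at least one non-case, which is about 41 of the 257.

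This is the only sample size basis in the article. If power is nearer 74% than 90%, the chance of missing the planned difference is about 26%, against the stated 10%. Section 1.2 intends the SMM results to inform recommendations for care. A reader who trusts the 90% would take more reassurance from a non-significant result than the design can support.

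**Working it through.** **Inputs (section 2.8).** p1 = 0.050 in S; p2 = 0.023 in K1 + K2; difference 0.027; odds ratio (0.050 × 0.977)/(0.950 × 0.023) = 2.24; 2 S and 3 K women per set; 257 sets.

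**Assumptions.** Two-sided 5%, inferred from the 95% confidence intervals in section 2.10; one-sided 5% is shown as well. No within-set correlation, because none is stated; a range follows in step 6.

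**1. Score test for a 2:3 set.** Let a be the cases among the 2 S women and t the cases in the whole set.
- Score contribution: U = a − 2t/5. Its mean is (6/5) × 0.027 = 0.0324.
- Null variance given t: 6t(5 − t)/100. Its expected value is V0 = 0.03924.
- Variance of U under the planned rates: V1 = 0.04499.
- Probability that a set is informative: about 1 − 0.950² × 0.977³ = 0.158, so 257 × 0.158 ≈ 41 sets.

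**2. The plan's figure.** N = [(z_α√V0 + z_β√V1)/E(U)]².
- Two-sided: [(1.960 × 0.1981 + 1.282 × 0.2121)/0.0324]² ≈ 415 sets.
- One-sided (z = 1.645): about 340 sets.
- Information form, (1.960 + 1.282)²/[ln(2.236)² × 1.2 × 0.0338 × 0.9662] = 414 sets, where 0.0338 is the pooled rate (one-sided 338).
- Null variance only: 393 sets (one-sided 320).

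The figure of 257 is not reproduced.

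**3. Power at 257 sets.** Power = Φ[(E(U)√N − z_α√V0)/√V1].
- Two-sided: (0.0324 × 16.03 − 1.960 × 0.1981)/0.2121 = 0.62, giving 73.2%.
- One-sided: 81.9%.
- Check by an unmatched two-proportion test, 514 against 771, pooled variance: 73.2% two-sided, 82.0% one-sided.

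**4. Simulation of the named test** (20,000 to 40,000 trials per run; type I error 5.0% at 257 sets).

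| Sets analysed | Two-sided | One-sided |
|---|---|---|
| 257 complete | about 74% (repeat runs 73.7% to 74.7%) | about 83% |
| 300 complete, no loss | about 80% | about 87% |
| 300 with 15% of women lost at random | about 71% to 72% | about 81% |
| 255 complete (15% of whole sets lost) | about 74% (formula 72.9%) | about 83% |
| 400 complete | about 90% | about 94% |
| 415 complete | about 91% (formula 90.0%) | about 95% |

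**5. S rate that would give 90% two-sided, with K at 23 per 1,000.** For 257 complete sets, 58 per 1,000 gives 89.5% and 59 gives 91.2% by simulation. For 300 sets with 15% of women lost, 58 gives 87.8%, 59 gives 89.5% and 60 gives 90.7%.

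**6. Within-set correlation.** A normal set effect was added on the logit scale, with the marginal rates held at 50 and 23 per 1,000. Two-sided power at 257 sets is 76% at SD 1, 78% at SD 1.5, 82% at SD 2 and 89% at SD 3. At SD 3 the intraclass correlation is about 0.33 and the conditional odds ratio is 3.51 instead of 2.24.

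**7. Drop-out step.** 257/0.85 = 302.4, so 303 sets against the 300 planned. With a drop-out of about 15% this is trivial and does not explain the gap.

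**The case against.** The strongest reply is that the calculation follows a cited method and a journal article condenses. An unstated input or software convention may lie behind 257. Some mixed conventions do come close. A one-sided level with a Breslow-type tie weight gives about 254 sets in log-odds form, or about 258 in a risk-difference form at the midpoint of the two rates. A one-sided log relative risk with the variance taken at 5.0% gives about 249. None returns 257, and they depart from the exact conditional test. The simulation in step 4 runs the named test directly, so its power does not depend on which planning formula was used.

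The second reply is that matching adds power. Section 2.5 stratifies on parity, singleton or twin pregnancy, and in- or outpatient recruitment, and says that risk differs across them. Some within-set dependence is therefore part of the design. Combined with a one-sided test, a logit SD of 2 gives about 89% at 257 sets and an SD of 2.5 about 91%. This stands as arithmetic. Those SDs are large, however, and the article states neither them nor a one-sided test.

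The third reply is that the harm is partly conjecture. This also stands in part: the article nowhere plans to read a non-significant result as no difference, and it already commits to odds ratios with confidence intervals.

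**Conclusion.** The concern holds with its conditions attached. From the inputs in section 2.8, 257 sets do not give 90% power on either sidedness. Power is about 74% two-sided and about 83% one-sided if there is no within-set correlation. Two-sided, the risk of missing the planned difference is about 26% at 257 sets and about 28% to 29% after random loss of 15% of women. One-sided, it is about 17% and 19%. The stated risk is 10%.

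A reader might infer three stronger things that the document does not support:
- That power is 74% without qualification. This rests on a two-sided test and on no correlation; the first is inferred and the second is assumed because none is stated.
- That the sponsor's calculation is shown to be in error. What is shown is that 90% does not follow from the inputs given. An undisclosed input could narrow the gap, but it would have to be very large.
- That the study must be enlarged. The shortfall concerns the stated power. It does not invalidate the planned model or its estimates.

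**What to change.** Keep the 1,500 women and correct section 2.8:
- State whether the 5% level is one- or two-sided, and give any within-set correlation used, with its justification.
- Unless a justified correlation supports 90%, restate the power for 50 against 23 per 1,000 as about 72% to 74% two-sided after 15% drop-out. The lower end applies if individual women are lost, the upper end if whole sets are lost.
- Equivalently, state 90% two-sided power for about 60 against 23 per 1,000 after drop-out (about 58 to 59 for 257 complete sets).
- Add a sentence that a non-significant SMM result will be read from the confidence interval for the odds ratio, and not as evidence of no difference.

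The cost is a few sentences and a less favourable stated power. Restoring two-sided 90% through numbers would instead take about 415 complete sets, or 415/0.85 ≈ 489 recruited sets (about 2,445 women). That is not proposed here.

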#### Additional group K2

2.3.3

Healthy pregnant women with a singleton fetus in cephalic presentation who register for birth at term after an uneventful course of pregnancy—i.e., low-risk women expecting an uncomplicated vaginal delivery—are invited for study participation as a second comparative group. No maternal pre-existing condition or obstetric complication, except for substituted hypothyroidism, must be present.

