**Figure 1 fig1:**
[figure not shown]
Overview of the recruitment and assignment process for study group S and groups K1 and K2.

Additionally, we stratified the recruited women as follows:

parity (nulliparous vs. parous);singleton vs. twin pregnancy; andoutpatient vs. inpatient recruitment.

The rationale for stratification is the difference in the risk profiles of nulliparous vs. parous women and singleton vs. twin pregnancies. The same applies for women requiring inpatient care vs. outpatient consultation.

For every pregnant woman recruited in S, the subsequent pregnant woman who presents at the study center and meets the inclusion criteria for K1 and K2 is invited to participate. To ensure a complete and continuous stratification process analogous lists are compiled, which are only accessible to the members of the research team and are carefully handled in accordance with data protection regulations.

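### The 15% drop-out allowance uses a proportional rule, but if women are lost singly 300 matched sets are worth about 244 complete sets under set-conditional analysis, not 257

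*Protocol article*

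**What the plan says.** The sample size in section 2.8 rests on severe maternal morbidity (SMM). The effect is given as "Assuming a SMM rate of 50 per 1,000 women in S and a SMM rate of 23/1000 in K1 + K2", and for the method "a score test established on a conditional logistic regression model was used". K1 and K2 are pooled, so a set has two S women and three comparators. The result is "257 matched sets of size 5 (2:3) are required to provide 90% power at a significance level of 5" per cent. The drop-out step follows: "Considering a drop-out rate of about 15%, 1,500 women in 300 matched sets of size 5 have to be recruited".

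Section 2.10 again names conditional logistic regression for the primary outcome, without saying which variable defines the conditioning sets, and adds: "The main analysis will be performed on complete cases". Section 2.5 describes how comparators are found: "For every pregnant woman recruited in S, the subsequent pregnant woman who presents at the study center" and who meets the K1 or K2 criteria is invited. It also lists three stratification factors: parity, singleton or twin pregnancy, and outpatient or inpatient recruitment.

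**The concern.** Dividing by one minus the drop-out rate is right when each retained woman contributes equally. Conditioning on sets of five breaks that. Each set pays a fixed price of one degree of freedom however many of its members remain, and a set left with only S women or only comparators contributes nothing. The members of a set are five separate women enrolled one by one, and under a complete-case analysis a woman without outcome data simply leaves her set. A 15% loss of women therefore removes more than 15% of the information, and the 300-set target falls short of the 257 complete sets on which section 2.8 bases its 90% power.

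**Working it through.** **Inputs.** From section 2.8: SMM rates 0.050 and 0.023, 2:3 sets, 257 sets, 90% power, 5% level, about 15% drop-out, 300 sets. From section 2.10: conditional logistic regression on complete cases. Assumed here: women are lost independently of one another at the same rate in all groups and are not replaced; the test is two-sided (section 2.8 does not state sidedness).

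**1. The plan's own drop-out step.** 257/0.85 = 302.4 sets, and 257 × 5/0.85 = 1,285/0.85 ≈ 1,512 women. The stated 300 and 1,500 agree with this to within rounding. Exactly, 1 − 257/300 = 14.3%. The rule gives the same total whether it is applied to sets or to women.

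**2. Information in one set.** With *a* S women and *b* comparators and a common event rate *p*, the expected conditional (hypergeometric) information is p(1 − p) × ab/(a + b). A full set has ab/(a + b) = 6/5 = 1.2.

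**3. After single losses.** Let each woman stay with probability q = 1 − d. Given that n women of the set remain, the mean of ab/n is 0.3 × (n − 1). Averaging over n and dividing by 1.2 gives the retained fraction (5q − 1)/4, apart from a negligible term for sets that vanish entirely. At d = 0.15 this is (4.25 − 1)/4 = 0.8125, against the 0.85 implied by the proportional rule. Direct enumeration over a ~ Bin(2, 0.85) and b ~ Bin(3, 0.85) gives the same 0.8125.

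| Loss of women | Retained fraction | 300 sets are worth | Power if 257 sets gave 90% |
|---|---|---|---|
| 10% | 0.875 | 262.5 | 90.6% |
| 12% | 0.850 | 255.0 | 89.8% |
| 14.3% | 0.821 | 246.3 | 88.7% |
| 15% | 0.8125 | 243.8 | 88.4% |

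The last column is Φ((1.960 + 1.282) × √(equivalents/257) − 1.960). Break-even solves (5q − 1)/4 = 257/300, so q = 0.885 and d ≈ 11.5%. Restoring 257 equivalents at 15% loss by recruitment alone would take 257/0.8125 = 316.3, that is 317 sets or 1,585 women.

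**4. Power at the stated rates.** For one full set the score has mean 1.2 × (0.050 − 0.023) = 0.0324, expected conditional variance 0.03924 and actual variance 0.04499. Two-sided 90% power then needs ((1.960 × √0.03924 + 1.282 × √0.04499)/0.0324)² ≈ 415 sets, and 257 sets give about 73%. Simulating the same score test (20,000 runs) gives:

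- 257 complete sets: 73.7%
- 244 complete sets: 72.0%
- 300 sets with 15% single losses: 71.9%

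A one-sided reading does not rescue the baseline: one-sided 90% needs about 340 sets, and 257 give about 82%.

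**5. Conditioning on cells instead of sets.** Parity, singleton/twin and recruitment setting form 2 × 2 × 2 = 8 cells, so about eight degrees of freedom are spent instead of up to 300. The retained information is then close to 300 × 0.85 = 255 set-equivalents. Simulated power is about 73.8% with equally likely cells and 73.5% with unequal ones. Both simulations keep the 2:3 mix in every cell.

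**The case against.** The strongest reply is that section 2.8 contains no calculation error: 300 and 1,500 are what the usual rule gives for about 15%. That stands.

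A reader might infer from the figures that drop-out was applied to whole sets, as if five women left together. The article does not say so. It gives the target in women and in sets, and the rule cannot tell the two apart. Whole-set loss at 15% would itself leave 255, so 2 of the 13 missing equivalents are rounding and only the step from 255 to 244 comes from single losses.

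The mechanism is also an assumption. The article says neither that losses are independent nor that they go unreplaced, and such detail may sit in the full protocol. Single loss is the natural reading for women enrolled one at a time, but the result depends on it and on the word about: at 12% loss the shortfall is two sets, and at 10% there is none.

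Only 0.85⁵ = 44% of sets would stay intact, and a reader might take that as the size of the damage. It is not. Section 2.8 describes a test that accepts varying numbers of cases and controls per set, so broken sets still contribute. The relevant comparison is 0.8125 with 0.85.

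Finally, K2 is restricted to "Healthy pregnant women with a singleton fetus in cephalic presentation who register for birth at term", and one might conclude that sets with a twin S woman are incomplete from the outset. The documents do not support this. K1 and K2 are pooled for the comparison, twins are not barred from K1, and the article does not say how such sets are filled.

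**Conclusion.** The point holds as a modest one. Under 15% independent, unreplaced loss of single women and conditioning on sets of five, 300 sets are worth about 244 complete sets. Relative to 257 that costs about 1.6 power points, taking a true 90% to about 88.4%. This alone would not undermine the study.

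It should not be read as the reason why 90% is missed. At the stated rates, two-sided power is about 72% after such loss and about 74% with 257 complete sets, so nearly all of the gap comes from the baseline. The 257 could not be reproduced from the stated rates, ratio, level and power. The cited method is not available here, so an input that the article omits may explain it. Correcting the drop-out step alone would not secure 90% power.

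**What to change.** Keep the recruitment target of 1,500 women.

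- **Section 2.8:** say whether the 15% refers to women or to sets and whether lost women are replaced. If women are lost singly and not replaced, give the power for 300 sets after that loss, at about 244 set-equivalents. Recompute the 257-set baseline in the same revision, with the sidedness and any further inputs stated.
- **Section 2.10:** name the conditioning variable. Conditioning the primary model on the existing stratification cells (parity, singleton or twin, recruitment setting, with calendar period if wanted) rather than on individual sets of five recovers roughly 255 set-equivalents from the same women.

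The cost is a restated figure and one or two sentences. The downside is looser matching on calendar time unless period is added. The gain will be somewhat smaller if cells are very unequal or if some contain no K2 women, as the twin cells will not. The conditioning variable should be fixed before outcomes are compared between groups.

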### Data collection and management

2.9

Trial data consist of three categories: medical outcome data, economic data, and questionnaires. Medical outcome is collected via database query of the hospital information system ORBIS (Dedalus Healthcare, Bonn, Germany), the ultrasound software ViewPoint™ (Version 6, GE HealthCare, Solingen, Germany), and the pediatric software Neodat (Version 5, Paedsoft, Tuebingen, Germany). Economic data are collected via database query of the information system SAP (SAP R/3 ECC 6.0, IS-H Release 617 Package, Walldorf, Germany). All questionnaires are completed online with the assistance of a study team member. Data management and monitoring is performed by the Clinical Support Study Center of the University Hospital Bonn, Bonn, Germany. All relevant trial data are entered in a specifically build REDCap© database (Version 12.0.27, Nashville, Tennessee, United States).

### Statistical analysis

2.10

All medical parameters will be summarized using descriptive statistics. The primary medical outcome will be analyzed with a conditional logistic regression model to assess the effects of pre-existing medical conditions on the SMM rate. Odds ratios obtained from this model with corresponding 95% confidence intervals will be reported. Further secondary medical maternal and perinatal parameters will be compared between the study and additional groups. Additional analyses of medical parameters will be considered in subgroups given by different pre-existing conditions in the study group and are exploratory in nature. The main analysis will be performed on complete cases and the significance level will be set to 0.05. A sensitivity analysis will include the use of multiple imputation strategies to address possible missing observations.

For analysis of costs, a health economic evaluation to determine the costs associated with the interventions and services in the different groups will be conducted. This includes, for example, consultation time, laboratory tests, medical procedures, hospitalization, or medication. The resource use of implemented care of all the three groups will be captured, both for inpatient and outpatient setting. Thereafter, this resource use will be multiplied times unit prices to derive respective costs from a provider (in-and outpatient healthcare provider) and healthcare system perspective (statutory health insurance).

The items of the questionnaires will be summarized descriptively at each time point. Health-related quality of life will be analyzed as pre-specified in the manual of the EQ-5D-5L™ tariff and compared over time (42). The birth experience assessed by the German version of the BSS-R will be reported via the total score and the three subscales (stress during labor, personal attributes, and quality of care provision) (39).

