### Background and rationale

1.1

The number of pregnancies in women with pre-existing medical conditions has increased over the last decades (1–3). A Danish registry study of more than 1.3 million births found an increase in the prevalence of maternal chronic conditions over a period of 25 years from 3.7% in 1989 to 15.7% in 2013 (1).

Three main factors contributing to this ongoing trend can be identified. First, the shift to delay childbearing resulting in advanced maternal age is associated with a higher prevalence of chronic conditions, such as cardiovascular diseases, obesity, or diabetes (4, 5). Second, advances in the treatment of severe childhood conditions result in higher life expectancy of affected women, who enter adulthood and may consider pursuing pregnancy. Improved survival rates of childhood, adolescent, and young adult’s cancers (6) or of newborns with congenital heart disease (7–9) may serve as examples. Lastly, progress in assisted reproductive technologies allows pregnancies in women with reduced fertility due to their advanced maternal age or pre-existing condition (10).

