### Trial design and study status

2.1

This study is designed as an observational, prospective, longitudinal single-center cohort study. Recruiting and data collection started in November 2022 and is scheduled to last until January 2024. Observation of participants covers the period from preconception counseling or initial consultation in pregnancy to hospital discharge after birth. Assignment to study and comparative groups is applied during recruiting.

This protocol is structured in accordance with the guidelines of Standard Protocol Items: Recommendations for Interventional Trials (SPIRIT)-Patient-Reported Outcomes (PRO)-Extension (33–35), although it is not considered an interventional trial. This extended version addresses the importance of patient-centered care by implementing recommendations to correctly document PRO in clinical trial protocols. In addition to this specific protocol writing guideline, we also applied aspects of the Strengthening the Reporting of Observational Studies in Epidemiology (STROBE) guidelines as this study is designed as an observational cohort study (36, 37).

Note on language usage: in this work we use the terms “woman/women” to refer to individuals with a uterus and the biological capacity to become pregnant.

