### Outcome measures

2.7

The three-dimensional design of the ForMaT-Trial indicates three different outcome measures as follows:

The primary medical outcome is SMM. For its assessment, a list with previously defined indicators can be found in Table 1. It was adapted from the Centers for Disease Control and Prevention (CDC) (15) after a thorough literature review. Maternal secondary outcome measures consist of complications of pre-existing disease or obstetric complications, mode of delivery, type of anesthesia, length of hospital stay for delivery, and need for transfusion >4 units of packed red blood cells (PRBC). Perinatal secondary outcome measures are late miscarriage (>14 weeks of gestation), intrauterine fetal death, gestational age at birth, birthweight with percentile, APGAR-scores, arterial umbilical cord pH, severe neonatal complications including transfer to NICU, length of stay in NICU, and death.In the second part of our study, an analysis of associated costs and reimbursement for study participants is undertaken. This includes the evaluation of billing and cost coverage of the in-and outpatient health sector and further associated costs.The third trial part captures the experience of pregnancy planning, pregnancy, and childbirth, as well as health-related quality of life in women with pre-existing disorders, which is assessed by questionnaires at predetermined time points (Figure 2). The questionnaires are a combination of pre-validated instruments and specifically designed questions. As validated PRO-instruments, the German version of the EQ-5D-5L™ is incorporated in each questionnaire (38) and the German version of the BSS-R (Birth Satisfaction Scale-Revised) is included in the postpartum questionnaire (39, 40). Table 2 provides an overview of item count, domains that are interrogated, and content of all four questionnaires. Questionnaires are only filled out by women in study group S. Timepoints are as follows (Figure 2): during the initial antenatal consultation at the study center; during the appointment for birth planning; and in the postpartum period before discharge from the maternity department. If the initial visit to the study center occurs after 34 weeks of gestation only one antenatal questionnaire is filled out. Recruited women seeking preconception counseling are also asked to fill out a questionnaire after the appointment.

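### The primary odds ratio is open to confounding by maternal age, which the protocol links to chronic conditions but neither stratifies on nor names for adjustment

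*Protocol article*

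**What the plan says.** All references are to the protocol article.

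- Section 2.1, design: "This study is designed as an observational, prospective, longitudinal single-center cohort study".
- Section 1.1, background. The first of three drivers of the rise in pre-existing conditions is that "the shift to delay childbearing resulting in advanced maternal age is associated with a higher prevalence of chronic conditions".
- Section 2.5, stratification factors: "parity (nulliparous vs. parous);singleton vs. twin pregnancy; andoutpatient vs. inpatient recruitment". The stated reason is that risk differs between these categories.
- Section 2.7: "The primary medical outcome is SMM".
- Section 2.8, sample size, on the score test used for sizing: "The test assesses the effect of a binary variable (= with/without pre-existing medical condition) on the outcome". K1 and K2 are pooled, giving matched sets of two S women to three comparison women.
- Section 2.10, primary analysis: SMM "will be analyzed with a conditional logistic regression model to assess the effects of pre-existing medical conditions on the SMM rate", with odds ratios and 95% confidence intervals. No covariate is named. The only sensitivity analysis named is multiple imputation for missing observations.

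**The concern.** Without randomisation, the comparison of S with K1 + K2 is protected only by what is matched on and what enters the model. The protocol accepts that baseline risk has to be balanced and chooses three factors for that purpose. Age is not one of them, although the protocol's own background ties it to the exposure. Women of the same parity, plurality and recruitment setting can still differ in age, so matching on those factors does not by itself balance it.

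If age also affects the risk of SMM and differs between the groups, the primary odds ratio mixes an age effect with the effect of the condition, while section 2.10 describes the result as an effect of the condition. Recruitment began in November 2022, so the matching factors are already in use and the model is the practical place left to deal with age. Age precedes both the later course of the condition and the outcome of the pregnancy, so adjusting for it does not remove part of the effect of interest.

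**Working it through.** **Inputs from section 2.8.** SMM 50 per 1,000 in S and 23 per 1,000 in K1 + K2; 257 sets of 2 + 3 women; 300 sets recruited. The 257 sets are taken as stated and used only to count women and events; whether they give the stated power is a separate question.

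**Planned odds ratio.** (0.05/0.95) / (0.023/0.977) = 0.05263/0.02354 = 2.236, about 2.24.

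**Expected events.** S: 257 × 2 = 514 women, 514 × 0.05 = 25.7. K1 + K2: 257 × 3 = 771 women, 771 × 0.023 = 17.7. Total 43.4. If all 300 sets were analysed: 600 × 0.05 + 900 × 0.023 = 50.7.

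**Size of a possible age bias.** The documents give neither the age-SMM association nor the share of older women in each group. Both are assumed below. With no true effect of the condition, the spurious ratio is

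(1 + pS(R − 1)) / (1 + pK(R − 1)),

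where pS and pK are the shares of older women and R is the ratio of SMM risk, older to younger. The last column divides 2.236 by the factor.

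| R | pS | pK | Factor | 2.236 / factor |
|---|---|---|---|---|
| any | 0.25 | 0.25 | 1.00 | 2.24 |
| 1.2 | 0.30 | 0.25 | 1.06/1.05 = 1.010 | 2.21 |
| 1.5 | 0.35 | 0.25 | 1.175/1.125 = 1.044 | 2.14 |
| 2.0 | 0.35 | 0.25 | 1.35/1.25 = 1.080 | 2.07 |
| 2.0 | 0.40 | 0.25 | 1.40/1.25 = 1.120 | 2.00 |
| 2.0 | 0.45 | 0.25 | 1.45/1.25 = 1.160 | 1.93 |
| 2.0 | 0.40 | 0.20 | 1.40/1.20 = 1.167 | 1.92 |
| 3.0 | 0.40 | 0.20 | 1.80/1.40 = 1.286 | 1.74 |

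SMM is rare, so working with odds ratios gives almost the same result (1.284 in the last row).

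**Direction.** If the comparison women were the older ones, the factor falls below 1. With R = 2.0, pS = 0.25 and pK = 0.35 it is 1.25/1.35 = 0.93.

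**False-positive rate.** Take a two-sided 5% comparison of 514 with 771 women, ignoring the matching, with SMM at 2.3% in K1 + K2 and no true effect. In the last row of the table the S rate becomes 2.93%. The difference is 0.0063, the pooled standard error 0.00898 and the unpooled one 0.00919. Upper tail: (0.0063 − 1.96 × 0.00898)/0.00919 = −1.23, probability 0.109. Lower tail: (−0.0063 − 1.96 × 0.00898)/0.00919 = −2.60, probability 0.005. The sum is 0.114 (0.115 with unrounded inputs). The same calculation gives 5.2% for R = 1.5 with 35% against 25%, 5.7% for R = 2.0 with 35% against 25%, and 7.4% for R = 2.0 with 40% against 20%.

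**The case against.** A reader might infer that the primary model is fixed with a single term, that S will be older, and that the odds ratio is therefore confounded. The article supports none of these three steps.

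- **Single term.** Section 2.10 names no covariates but does not exclude them. The single binary variable in section 2.8 describes the test used for sizing, and sizing on the exposure alone does not fix the analysis model. Conditional logistic regression takes age as a covariate without contradicting the text.
- **S older.** Section 1.1 explains a population trend. Its second driver is survival after severe childhood disease, which need not mean older mothers, and section 3 reports that 33.8% of women aged 18–29 have a long-term condition. K1 makes up two thirds of the pooled comparator under the 2:2:1 ratio and is selected for obstetric risk, so it may be as old as S. Stratifying on parity may also reduce an age difference.
- **Confounded.** This also needs age to affect SMM, and the article does not say that it does.

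In addition, a covariate list usually belongs in an analysis plan or full protocol, which is not shown here, and section 1.2 describes the study's aim as descriptive.

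These objections limit the claim to openness to confounding. They do not remove it. The article states its balancing factors, its primary model and its sensitivity analysis, speaks of effects, and in none of these places takes up a variable that it ties to the exposure itself. If the analysis plan already adjusts for age, a confirmation settles the point.

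**Conclusion.** The point holds in a limited form: the primary odds ratio is open to confounding by maternal age unless a document not shown adjusts for it. Neither the size nor the direction of a bias can be read from the article. If S is assumed older, with an age risk ratio of 1.2 to 3.0 and shares of older women of 30–45% in S against 20–25% in K1 + K2, the spurious ratio is about 1.0 to 1.3. The upper end needs both a strong age effect and a large imbalance; with equal age distributions there is no bias. Age alone would not explain an odds ratio of 2.24, which would still be about 1.7 to 2.2 after adjustment. It could matter more for a smaller observed effect, or for a result near the significance limit. The change is worth making because it is cheap, not because the primary result is shown to be wrong.

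**What to change.** In section 2.10, prespecify maternal age at recruitment as a continuous covariate in the primary conditional logistic model and report the unadjusted odds ratio beside the adjusted one. If the analysis plan already does so, confirm it. This should be settled before outcome data are examined, since choosing covariates afterwards with so few events would be harder to defend.

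The cost is one sentence, one extra parameter on about 43 expected events, and a slightly wider interval. Age should be obtainable from the hospital information system named in section 2.9, although that section does not list it. The groups, the stratification and the recruitment stay as they are.
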